### Control group

The interventionist will provide the control group feedback on a summary of the results of the baseline survey (employee and workplace questionnaire) and information on existing materials on evidence-based smoking cessation measures (i.e., promoting utilization of smoking cessation treatment and implementing smoke-free workplaces). The timing of the feedback provision will be aligned with each completed employee questionnaire.

As a usual practice, both the intervention and control groups will receive workplace health promotion support and individual health guidance for targeted employees from health nurses in the JHIA.

### Outcomes

We will evaluate the health-, implementation-, process-, and cost-related outcomes. Outcome measures, evaluation period, and data sources are summarized in Table 2.

**Table 2 Tab2:** Outcome measures by period and data source

	Baseline	Follow-up		
Outcome measures		6 months	12 months	Data source
Health outcomes				
Smoking status	〇	〇	〇	Employee questionnaire
Cotinine-validated 7-day point-prevalence abstinence rate		〇	〇	Employee questionnaire Biochemical test
30-day point-prevalence of smoking abstinence		〇	〇	Employee questionnaire
Three-month point-prevalence abstinence rate		〇	〇	Employee questionnaire
Six-month point-prevalence abstinence rate			〇	Employee questionnaire
Three months prolonged abstinence rate		〇	〇	Employee questionnaire
Six months prolonged abstinence rate			〇	Employee questionnaire
Proportion of nicotine patches and gum use		〇	〇	Employee questionnaire
Proportion of quit attempts	〇	〇	〇	Employee questionnaire
Number of cigarettes or capsules	〇	〇	〇	Employee questionnaire
Implementation outcomes				
Adoption of two recommended measures	〇	〇	〇	Workplace questionnaire
Penetration of smoking cessation clinic visits		〇	〇	Employee questionnaire
Process outcomes				
Adherence (content) (e.g., Was each recommended measure implemented as planned?)	●	●	●	Workplace tobacco control checklist Interventionists’ notes
Adherence (frequency/duration) (e.g., Were the recommended measures implemented as often and for as long as planned?)		●	●	Health manager’s logbooks Interventionists’ notes
Adherence (coverage) (e.g., What proportion of employees who smoke participated in the cessation campaigns?)		●	●	Health manager’s logbooks Interventionists’ notes
Potential moderators (responsiveness) (e.g., How did employees who smoke engage with the smoking cessation campaigns?)		●	●	Semi-structures interviews Interventionists’ notes
Potential moderators (complexity) (e.g., How complex is the intervention?)		●	●	Semi-structures interviews Interventionists’ notes
Potential moderators (comprehensiveness) (e.g., How specific is the interventions description?)		●	●	Semi-structures interviews Interventionists’ notes
Potential moderators (strategies) (e.g., What strategies were used to support implementation?)		●	●	Semi-structures interviews Health manager’s logbooks Interventionists’ notes
Potential moderators (quality) (e.g., How was the quality of the delivery of intervention components?)		●	●	Semi-structures interviews Health manager’s logbooks Interventionists’ notes
Potential moderators (recruitment) (e.g., What constituted barriers to maintaining involvement of employees?)		●	●	Semi-structures interviews Health manager’s logbooks Interventionists’ notes
Potential moderators (context) (e.g., What factors at political, economic, organizational, and work group levels affected the implementation?)		●	●	Semi-structures interviews Health manager’s logbooks Interventionists’ notes
Cost outcomes^a^				
Employees’ direct medical costs		〇	〇	Health Insurance database
The mean values and response rates for basic health check-up items		〇	〇	Health Insurance database
Workers’ lost productivity (absenteeism, presenteeism)	〇	〇	〇	Employee questionnaire
Cost of implementing tobacco control measures		〇	〇	Health manager’s logbooks

Black circles refer to collecting data for the intervention group only, and white circles refer to data collection for both groups

^a^Cost outcome measures will be collected throughout the year from baseline to 12 months

#### Health outcomes

The primary health outcome will be the salivary cotinine-validated 7-day point-prevalence abstinence rate 6 months after the initial session, according to the Russell Standard [29]. Abstinence rate will be assessed by self-reporting using an employee questionnaire with the following questions: “Have you smoked even one mouthful of tobacco [including all cigarettes, (cigarettes rolled in paper, heated, and other types)] in the last seven days?” Seven-day point-prevalence is defined as salivary nicotine-confirmed self-reported tobacco cessation in the last 7 days (response of “no” to the above question), and a cotinine concentration of 15 ng/ml or less will verify self-reported smoking abstinence [30]. A Smokerlyzer will be used to measure expired air carbon monoxide concentrations, with a cut-off point of six parts per million if self-reported quitters report using a nicotine patch or gum within 7 days of the salivary cotinine measurement date [31]. If an employee’s self-reported smoking abstinence does not match the biochemical measurement, the employee will be classified as a smoker.

Other health outcomes include the salivary cotinine-validated 7-day point-prevalence abstinence rate 12 months after the initial session, 30-day point-prevalence abstinence rate at 6 and 12 months, 3-month point-prevalence abstinence rate at 6 and 12 months, 6-month point-prevalence of abstinence rate at 12 months, the proportion of quit attempts at 6 and 12 months, and the number of cigarettes or capsules at 6 and 12 months among employees who report being smokers at the baseline survey. Among employees who smoke and declare to quit during the intervention period in the intervention group, the 3 months prolonged abstinence rate at 6 and 12 months, and 6 months prolonged abstinence rate at 12 months will be measured. In addition, we will assess the proportion of nicotine patches and gum use in the past 6 and 12 months measured at 6- and 12-month follow-ups, respectively, among employees who smoke at baseline.

Furthermore, the mean values and response rates for basic health check-up items (medical interview sheet, physical measurements, blood pressure, blood lipids, liver function, blood glucose, and urine) in all employees or in the smoking population will be obtained from the JHIA headquarters after each SMEs’ employer agrees.

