### Intervention

The intervention will be provided for employers and health managers in each of the participating enterprises over 6 months. Interventionists will be three research team members (MO, TS, and JS) specializing in psychology, medicine, and nursing, respectively. The team member who specializes in psychology will train the other two interveners in advance using the intervener manual. The manual provides examples of dialogs with employers and health managers, as well as various combinations of behavior modification approaches that should be offered for each factor.

As shown in Table 1, the intervention will consist of a bundle of three implementation strategies (supporting employees through campaigns, tailored ongoing facilitation, and ensuring executive engagement and support), developed based on our prior work, which demonstrated that strong endorsement, support, and positive feedback from employers are important to promote the implementation of workplace health promotion [13]. It also identifies strategies for the prevention of non-communicable diseases for SMEs in Japan following an implementation mapping protocol [26]. These three implementation strategies will be provided through five steps in web-based sessions, with four sessions for employers and ten sessions for health managers (maximum of 16) (Fig. 2). In principle, the sessions will be conducted online using a web conferencing system but may be conducted in person if the situation warrants. From 1 month after the intervention begins, each enterprise will be required to start the smoking cessation campaign with an option of the incentives for successful quitters. As multi-level interventions are more effective, if a complete smoke-free policy is not in place, it is recommended that they are implemented at the same time as, or around the time of, the launch of the campaign.

**Table 1 Tab1:** Implementation strategies

Implementation strategy	Description	ERIC category	Description according to Proctor [27]	

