#### Questionnaire

Data from the employee questionnaires will be collected electronically using the electronic data capture system ViedocMe (Viedoc Technologies, Sweden) established by the data center. The QR code of the URL of this survey form will be printed and distributed to each employee, along with their individual account ID and password. During the predefined questionnaire response period, employees will log in using their individual account ID and password on the web page or by using an application on a smartphone or tablet device and then complete the survey. Once logged in, a check box will ask whether the participants agree to complete the survey, after an introduction to this project and the survey. If an employee selects the “Disagree” box, the survey form will be closed. If enterprises desire, printed paper responses will also be accepted. Saliva will be collected by mail from employees who report they have not smoked in the past 7 days at the 6- and 12-month follow-up [34]. Data from the workplace questionnaire and workplace tobacco control checklist will be collected electronically using survey applications, such as Google Forms and Microsoft Forms.

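### The 30-day, 3-month and 6-month abstinence rates rest on questionnaire alone, although a biochemical test is planned at the same follow-up for everyone who could meet them

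*Protocol article*

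**What the plan says.** In Table 2 (Outcomes), the source for the 7-day rate is "Employee questionnaire Biochemical test". The rows "30-day point-prevalence of smoking abstinence", "Three-month point-prevalence abstinence rate" and "Six-month point-prevalence abstinence rate" name the employee questionnaire only. The Health outcomes text agrees. Its list of other outcomes describes the 12-month 7-day rate as cotinine-validated and then gives "30-day point-prevalence abstinence rate at 6 and 12 months, 3-month point-prevalence abstinence rate at 6 and 12 months", and the 6-month rate at 12 months, without that qualifier.

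The Questionnaire section states: "Saliva will be collected by mail from employees who report they have not smoked in the past 7 days at the 6- and 12-month follow-up". The Biochemical test section makes this conditional on verbal consent by telephone and on return of a kit. Health outcomes sets the cotinine limit at 15 ng/ml, and adds expired CO with a 6 ppm cut-off for recent patch or gum users. The paragraph defining the primary outcome ends with a rule that an employee whose self-report disagrees with the biochemical result is treated as a smoker. It does not say whether this reaches the other abstinence outcomes.

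**The concern.** The longer windows are the stricter definitions of abstinence, yet they carry the weaker verification. On the plain reading, one employee at one follow-up can be a smoker under the 7-day outcome and a quitter under the 3-month outcome.

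These rates matter because they are the only between-arm abstinence rates with a window longer than 7 days. The Health outcomes text confines the prolonged-abstinence rates to declared quitters in the intervention group. (Table 2 marks those rows as collected in both groups, but they too are questionnaire-only.)

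False reporting could plausibly differ by arm. The protocol describes the cessation campaign, "with an option of the incentives for successful quitters", and the health manager's regular follow-up of declared quitters only as parts of the intervention. Employers and health managers know their allocation.

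**Working it through.** **Nesting.** A point-prevalence window ends at the survey. Someone with no smoking in the past 30 days, 3 months or 6 months therefore has none in the past 7 days, and belongs to the group from whom saliva is to be requested at that follow-up. The verifying result is planned but not used for these outcomes.

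**When the order reverses.** Among tested employees, let V be the validated 7-day quitters, L those of V who also report the longer window, and F those who report the longer window but fail validation. The 7-day count is V and the longer-window count is L + F. The longer-window count is the larger whenever F > V − L. True abstinence cannot behave this way, because the windows are nested.

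**Size.** The documents give no false-report rate, so the rates below are assumptions: 2–10% of continuing smokers in the intervention arm and 1–5% in control. The 7-day planning rates from Sample size and power calculations (13.3% and 3.7%) stand in for the longer windows. With true rate p and false-report rate r among continuing smokers:

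observed rate = p + (1 − p) × r

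No true effect (3.7% in both arms), so the spurious difference is 0.963 × (r₁ − r₀):
- 5% v 2%: 0.037 + 0.963 × 0.05 = 8.5%; 0.037 + 0.963 × 0.02 = 5.6%; difference +2.9 points
- 2% v 1%: 5.6% v 4.7%; about +1.0 point
- 10% v 1%: 13.3% v 4.7%; +8.7 points
- 2% v 5%: 5.6% v 8.5%; −2.9 points

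Planned effect (13.3% v 3.7%, difference 9.6 points):
- 5% v 2%: 0.133 + 0.867 × 0.05 = 17.6%; minus 5.6% = 12.0 points
- 5% v 5%: 17.6% − 8.5% = 9.1 points
- 2% v 5%: 0.133 + 0.867 × 0.02 = 15.0%; minus 8.5% = 6.5 points

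**Another way to set the assumption.** If instead a share f of self-reported quitters fails validation, observed rate = validated rate / (1 − f). At f = 20% in both arms: 0.133 / 0.8 = 16.6% and 0.037 / 0.8 = 4.6%, a difference of 12.0 points. So equal false reporting shrinks the difference when expressed per continuing smoker and enlarges it when expressed per claimed quit. The direction depends on an assumption that the documents do not settle. The inconsistency between outcomes does not.

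**The case against.** The strongest reply is that the mismatch rule speaks of the employee and not of one outcome, so it may already reclassify anyone who fails validation across all abstinence outcomes. That reading is open. But Table 2 then contradicts it by listing no biochemical source for the longer windows, and the same amendment is needed. The protocol also leaves detailed methods for secondary outcomes to a statistical analysis plan that is not shown. That plan could settle the scoring, but the data source is fixed in the protocol itself.

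Several stronger readings are tempting and are not supported:
- A reader might infer that the self-report rates are biased towards the intervention. The assumed ranges allow about −2.9 to +8.7 points under no effect. There are also features that limit pressure: employees answer under individual log-ins, enterprises are told not to force anyone to quit, incentives are optional, and the weekly contact concerns declared quitters only.
- A reader might infer that every longer-window quitter will have a test result. Testing is planned, but consent can be refused and kits may not come back.
- A reader might infer that cotinine above 15 ng/ml always means a smoker. Recent patch or gum users are assessed by expired CO.
- A reader might infer that every claim of lasting cessation rests on these rates. The validated 7-day rate at 12 months is also between-arm evidence of later cessation.

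One practical objection stands. The primary analysis includes only those with 6-month biochemically confirmed data. Copying that rule would drop self-reported quitters who return no kit, while self-reported smokers need no kit.

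**Conclusion.** The point holds as a matter of outcome definition. Three between-arm secondary outcomes are set on questionnaire alone when a test is planned at the same follow-up for everyone who could meet them. As written, they can disagree with the validated 7-day outcome for the same person and can exceed it in aggregate. This rests on the plain reading of Table 2 and Health outcomes, and on the windows ending at the survey.

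The size and sign of any bias between arms are not established. The 2.9-point figure is an illustration under assumed rates of 5% versus 2%, with 7-day planning rates standing in for the longer windows. The primary outcome and sample size are not touched. It is worth correcting because the correction is cheap, not because a bias in one direction has been shown.

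**What to change.** Define the 30-day and 3-month rates (at 6 and 12 months) and the 6-month rate (at 12 months) as self-report plus a passed biochemical test from the same follow-up: cotinine, or CO for recent patch or gum users. State that the mismatch-means-smoker rule applies to them, and add the biochemical test as a source in those three rows of Table 2. Report the self-report versions as sensitivity results. Add an analysis that counts self-reported quitters without a test result as smokers, so that the comparison does not hinge on dropping people whose kits were not returned.

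No new sample or visit is needed. The cost is slightly lower abstinence figures and some test-related missing data. A passed test confirms only recent abstinence: it removes current smokers but cannot prove the length of the quit. Trial status reports that 12-month evaluation was under way and analysis had not begun at first submission, and the protocol promises the secondary-outcome methods before the data are fixed, so the analysis plan is the natural place for the change.

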#### Implementation outcomes

Implementation outcome is defined as “the effects of deliberate and purposive actions to implement new treatments, practices, and services,” and serves as indicators of the implementation success, showing progress in implementation processes, and as key intermediate outcomes related to health outcomes [32]. The primary implementation outcome in this study will be the adoption of two recommended measures (promoting utilization of smoking cessation treatment and implementing smoke-free workplaces) at 6 months (binary outcome) obtained from the workplace questionnaire that collects data at the worksite level.

Other implementation outcomes will include the adoption of two recommended measures at 12 months, and the penetration of smoking cessation clinic visits during the past 6 and 12 months among employees who report smoking at baseline, which will be evaluated using self-report responses from employee questionnaires at 6 or 12 months. The penetration is defined as “the number of eligible persons who use a service, divided by the total number of persons eligible for the service [32],” and could also be called in this study as the proportion of those who visited a smoking cessation clinic at least once during the intervention period among employees who smoked at baseline.

#### Process outcomes

For process outcomes, we will apply the modified conceptual framework for implementation fidelity by Hasson to select the process evaluation of the fidelity of implementation strategies that the employer and health manager are required to implement during the intervention: adherence and potential moderators [33]. Table 2 presents the components addressed: adherence (e.g., content and frequency or duration) and potential moderating factors (e.g., participant responsiveness, intervention complexity, comprehensiveness of policy description, and strategies to facilitate implementation). We will assess these components only in the intervention groups.

#### Cost-related outcomes

The cost-effectiveness of workplace smoking cessation will be estimated as the incremental cost per quit in the intervention group versus the control group over the intervention and follow-up periods (12 months after the initial session). The cost component accounts for three categories: (1) the cost of implementing tobacco control measures in the workplace, (2) employees’ direct medical costs during the study period, and (3) workers’ lost productivity.

The cost of implementing the measures includes the amount of time spent by employers and health managers on implementing the measures, converted into labor costs using the average salary level for the relevant age group in Japan, as well as cost for incentives, including cost assistance schemes for smoking cessation treatments, and the implementation of smoke-free policies. Employees’ direct medical costs consist of medical treatment costs (calculated from the total number of points in the monthly medical fee schedule) and medical expenses (calculated from the monthly total of the medical remuneration statement). Workers’ lost productivity will be estimated based on absenteeism and presenteeism. Absenteeism is the loss of productivity due to absence from work; the amount of labor cost loss will be calculated by converting the number of days of absence from work owing to sickness (from the questionnaire) into labor costs at the average salary level for the relevant age group in Japan. Presenteeism refers to the loss of productivity at work owing to an illness and performing at lower levels than usual. The amount of labor cost loss will be calculated by converting relative presenteeism [i.e., a ratio of actual performance to the performance of most workers at the same job (possible performance) from the World Health Organization Health and Work Performance Questionnaire, Japanese edition] into labor costs at the average salary level for the relevant age group in Japan.

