**Methods:**

This hybrid type II cluster randomized effectiveness implementation trial (eSMART-TC) aims to examine the effects of interactive assistance for SME management on health and implementation outcomes. We will provide interactive assistance to employers and health managers for 6 months, aiming to promote the utilization of reimbursed smoking cessation treatments by public health insurance and to implement smoke-free workplaces. The intervention will consist of three strategies: supporting employees through campaigns, tailored ongoing facilitation, and ensuring executive engagement and support. The primary health and implementation outcomes will be salivary cotinine-validated 7-day point-prevalence abstinence rate, and the adoption of two recommended measures (promoting utilization of smoking cessation treatment and implementing smoke-free workplaces) 6 months after the initial session, respectively. Other outcomes for implementation (e.g., penetration of smoking cessation clinic visits), health (e.g., salivary cotinine-validated 7-day point-prevalence abstinence rate at 12 months), and process (e.g., adherence and potential moderating factors) will be collected via questionnaires, interviews, logbooks, and interventionists’ notes at 6 and 12 months. An economic analysis will be undertaken to assess the cost-effectiveness of the implementation interventions at 12 months.

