#### Cost-related data

Health managers’ logbooks will be used to estimate the costs of implementing tobacco control measures in the workplace. For data on the direct medical costs of employees during the study period, the mean values for all employees or the smoking population in each SME will be obtained from the health insurance database at JHIA headquarters after obtaining each SMEs’ employer agreement. Finally, an employee questionnaire will be used to assess workers’ lost productivity. All data will be stored securely and will only be accessible to the research team and data manager.

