The incremental cost per quit will be estimated as the cost per smoker in the intervention group minus the cost per smoker in the control group divided by the incremental quit between the intervention and control groups. Probabilistic and deterministic sensitivity analyses will be performed to quantify the uncertainties associated with the input parameters and to assess the robustness of the base case. The deterministic analysis will assume a percentage variation of respective cost parameters from the base case. Monte Carlo simulation will be applied to conduct probabilistic sensitivity analysis by varying the input parameters based on the appropriate distributions.

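### The incremental cost per quit has no cost line for delivering the assistance under test, so as written it understates that cost; the population for medical costs is also left open

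*Protocol article*

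**What the plan says.** The abstract (Methods) sets the purpose: "An economic analysis will be undertaken to assess the cost-effectiveness of the implementation interventions at 12 months". Cost-related outcomes then lists what is counted: "The cost component accounts for three categories: (1) the cost of implementing tobacco control measures in the workplace", followed by employees' direct medical costs and lost productivity. The first category is spelled out: "The cost of implementing the measures includes the amount of time spent by employers and health managers on implementing the measures", together with incentives (including help with treatment costs) and smoke-free policies. Its source is given under Cost-related data: "Health managers’ logbooks will be used to estimate the costs of implementing tobacco control measures in the workplace". Table 2 names the same single source.

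The assistance itself is described under Intervention. "Interventionists will be three research team members", from psychology, medicine and nursing, deliver it "with four sessions for employers and ten sessions for health managers (maximum of 16"). One of them trains the other two beforehand. Table 1 adds further contact by e-mail and phone when needed. Under Control group, control enterprises receive a summary of survey results and existing materials.

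Statistical analysis defines the numerator of the ratio as "the cost per smoker in the intervention group minus the cost per smoker in the control group". For medical costs, Cost-related data says that "the mean values for all employees or the smoking population in each SME will be obtained from the health insurance database", without saying which of the two enters the ratio.

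**The concern.** The interventionists' work is the resource that randomisation adds. An enterprise or insurer taking up the programme would need someone to do that work. If it has no cost line, the analysis counts the quits that the assistance produces but not the assistance. The Background calls cost-effectiveness and budget impact important to organisations' decisions, and the Discussion looks ahead to wide adoption, so readers would take the ratio as the price of the programme.

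The second, smaller matter is the unit of analysis. A per-smoker ratio needs costs for smokers. If an enterprise mean over all employees were used in its place, a change confined to smokers would be diluted.

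**Working it through.** The article states no cost, wage or cost-per-quit figure, so there is nothing of its own to reproduce. The check has three parts.

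**1. Is there a place for delivery cost?**
- The three categories cover what the enterprise does, medical care and lost productivity.
- The only source for implementation cost is the health managers' logbooks. Under Other data sources, these record the health managers' own tobacco-control actions.
- Table 2 uses interventionists' notes for process outcomes only, not for cost.
- So neither the categories nor the sources capture interventionist time.

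**2. How much time is left out?** Inputs:
- Session time per enterprise (Discussion): employer 4–6 h, health manager 6.5–9 h.
- Smokers per enterprise (Sample size): 50 × 0.30 = 15.
- Abstinence (Sample size): 13.3% against 3.7%, a difference of 0.133 − 0.037 = 0.096.

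Extra quits per enterprise = 15 × 0.096 = 1.44.

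Contact hours per enterprise depend on how many sessions employer and health manager attend together:
- Shorter end, all employer time joint: 6.5 h. Per smoker 6.5 / 15 = 0.43 h; per extra quit 6.5 / 1.44 = 4.5 h.
- Shorter end, none joint: 4 + 6.5 = 10.5 h; per extra quit 10.5 / 1.44 = 7.3 h.
- Longer end, none joint: 6 + 9 = 15 h. Per smoker 15 / 15 = 1.0 h; per extra quit 15 / 1.44 = 10.4 h.

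Over 18 intervention enterprises this is 18 × 6.5 = 117 h to 18 × 15 = 270 h, before preparation, messages and training.

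With an assumed JPY 2,000–10,000 per hour (the article gives no rate), the omitted cost per extra quit runs from 6.5 × 2,000 / 1.44 = JPY 9,028 to 15 × 10,000 / 1.44 = JPY 104,167.

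**3. What would the choice of medical-cost population do?** Assume non-smokers' costs do not differ between arms. The all-employee difference is then 0.30 times the smokers' difference. Take an assumed difference of JPY 5,000 per smoker:
- Smokers' costs higher under intervention: the medical part per quit is 5,000 / 0.096 = JPY 52,083 with smokers' means and 0.30 × 5,000 / 0.096 = JPY 15,625 with all-employee means. The intervention looks cheaper.
- Smokers' costs lower: −52,083 becomes −15,625. The intervention looks dearer.

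With smokers' means there is no mismatch.

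**The case against.** **Perspective.** Aim 3 and Cost-related outcomes name workplace cessation as the object, and the Background speaks of organisations' decisions. Interventionists belong to the research team, so on a strict enterprise view their time is not a workplace cost. That view would be defensible if declared. It is not declared, it sits badly with the abstract, and the inclusion of medical costs drawn from the insurer's database points to something broader than the enterprise.

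**Open wording and condensation.** The sentence on implementation cost lists what is included and is not strictly exhaustive. The article also leaves detailed methods for cost outcomes to an analysis plan that is not shown. But the article does not merely stay silent: it sets out the categories, their contents, how they are valued and where the data come from. Delivery fits none of these.

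**Materiality.** This objection stands in part. The hours per quit use 6-month planning rates while the ratio is at 12 months, the lowest bound supposes every employer session is joint, and no unit cost is given. Per smoker the omitted contact is 0.43–1.0 h, about 0.02–0.06% of an assumed 1,600–2,000 working hours a year, in a calculation that includes a year of productivity loss. Against that, the numerator is a difference between arms, in which most of the year's labour cost should cancel while the omitted time does not.

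**Medical costs.** A reader might infer that all-employee medical costs will be put into the per-smoker ratio and that this too favours the intervention. The text does not support either step. It offers all employees or smokers without choosing, and dilution can move the ratio up or down. The 0.30 factor also assumes no effect on non-smokers, although the Background notes that smoke-free policies reduce secondhand smoke.

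**Conclusion.** The point holds for delivery cost. As written, the incremental cost per quit has no category and no data source for the assistance being tested, and no stated perspective excuses this. The omitted cost is positive and arises almost wholly in the intervention arm, so the ratio is understated, provided the intervention arm has more quitters. About 4.5–10.4 interventionist contact hours per extra quit is an illustration resting on planning values; the direction does not depend on it. The documents do not show that the omission would change the economic conclusion, and that should not be claimed.

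The population for medical costs is an unresolved choice rather than an error already made, and the direction of any bias from it is undetermined. Both matters concern Aim 3 and leave the two primary outcomes untouched.

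**What to change.** 1. State the perspective of the economic analysis.
2. Add interventionist delivery as a cost category in the base case: sessions, preparation, e-mail and phone support, and training. Take session time from the session schedule and interventionists' notes. Nothing in the article shows that the other time was recorded, so estimate it where it was not, say how, and vary it in the planned deterministic and probabilistic sensitivity analyses. Cost the control arm's feedback in the same way.
3. Report the ratio without delivery cost as a sensitivity analysis, labelled as enterprise/payer cost.
4. Define the population for medical costs as baseline smokers in both arms. The article does not say how or when the insurer's smoking population is determined. If it were determined at follow-up, quitters would drop out of the costs, so asking for the smokers' mean without fixing the date is not enough.

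The cost is a modest amount of extra costing work, some of it retrospective because 12-month evaluation was under way when the article was submitted. Analysis had not begun at that point. The reported cost per quit will be less favourable than it would be without the delivery line.
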